**Fig. 2 Fig2:**
[figure not shown]
Inclusion procedure flowchart. AOM, acute otitis media; ENT, ear, nose and throat; OME, otitis media with effusion

We will include children aged 9–36 months. Infants younger than this age group require special anaesthesiological care, which cannot be offered in Greenland for ventilation tube insertion. The upper age limit has been set as low as possible in order to intervene before progression of the disease, while ensuring adequate sample size in this small population. We have attempted to reduce the number of exclusion criteria to as few as possible. However, children with orofacial cleft, Down’s syndrome and immune deficiency are, for other reasons, known to be at very high risk of chronic otitis media with effusion and recurrent acute otitis media and are therefore not comparable with other children. Children already treated with ventilation tubes can also not be included.

### Trial site and personnel

The trial sites are hospitals and health clinics in six Greenlandic towns: Nuuk, Sisimiut, Ilulissat, Aasiaat, Qaqortoq and Tasiilaq. The Greenlandic health-care system is divided into primary and secondary sectors. The only large and secondary referral hospital is in the capital, Nuuk [27].

The personnel performing the initial selection and screening of participants will be the regular staff at the Greenlandic health clinics and hospitals, for instance nurses, assistants and doctors of different specialities and ranks.

### Randomization

The enrolment of patients will be conducted by an ear, nose and throat (ENT) specialist and the coordinating investigator. We will use centralized stratified web-based randomization. Prior to randomization, a computer will generate randomization sequences with varying block sizes that are unknown to the investigators. An internet-based randomization system will be set up conducting randomization stratified according to centre (trial site) and type of otitis media, i.e., recurrent acute otitis media or chronic otitis media with effusion at baseline (yes or no). The randomizing investigator will access the internet site through a personal information number. Patients who meet both criteria for chronic otitis media with effusion and recurrent acute otitis media will be considered in the recurrent acute otitis media group. The patients will be randomly allocated 1:1 into the two intervention groups.

### Interventions

The experimental intervention consists of bilateral insertion of ventilation tubes (Donaldson) in the tympanic membranes, administered under general anaesthesia.

Short-term ventilation tubes will be used, consistent with the tube type applied in the majority of other studies, and in accordance with the type that is expected to be introduced in Greenland [18, 23]. If the tympanic membrane is infected at the time of ventilation tube insertion, topical antibiotics will be given (Cilodex® [dexamethasone + ciprofloxacin] eardrop suspension, 3 mg + 1 mg, dexamethasone + ciprofloxacin) at a dose of four drops twice daily for 5 days.

If children in the intervention group seek medical assistance for ear problems after the insertion of ventilation tubes, these ear problems will be treated according to current practice in Greenland, which includes systemic antibiotic treatment (amoxicillin 40–90 mg/(kg day)), as well as aural toilette and topical antibiotics (ciprofloxacin 1 ml/3 mg, three drops, twice daily, or Cilodex® [dexamethasone + ciprofloxacin] eardrop suspension, 3 mg + 1 mg, four drops twice daily for 5–7 days).

The control intervention will be based on the current practice in Greenland, which includes systemic antibiotic treatment (amoxicillin, 40–90 mg(kg day)), as well as aural toilette and topical antibiotics (ciprofloxacin 1 ml/3 mg, three drops, twice daily). Children in the control group will not be offered ventilation tubes for any circumstance until at least 2 years after the first ENT visit and randomization.

Children in both the intervention group and control group will have an ENT examination, including otoscopy by an ENT specialist at least once a year and at the end of the study period, 2 years after randomization.

### Outcomes

To assess the primary outcome in as unbiased a manner as possible, it is necessary to choose an outcome that does not require visualization of the tympanic membrane, as this might reveal the trial intervention allocation of the patient (the ventilation tube or sequelae to such a tube would be visible). Therefore, the primary outcome will be the number of visits to health clinics during 2 years after randomization, determined according to the medical records, assessed blinded to intervention. In otherwise healthy children, the number of visits to health clinics can be assumed to reflect the number of episodes related to the ear or upper respiratory tract, as this is thought to be the primary reason for contact to health clinics for children aged 9–36 months [28].

It is currently not possible to assess hearing level as an outcome measure because there are no facilities available in Greenland able to meet the high standard of hearing evaluation, which would be necessary to detect differences in hearing levels of 4 dB [23]. We therefore postulate that an effect of ventilation tubes on otitis media with effusion might be reflected in a change in the number of visits to health clinics. The number of episodes of acute otitis media, based on medical records, will be included as a secondary outcome measure but will not be used as a primary outcome measure because the treatment providers and the outcome assessors will often not be sufficiently blinded to the trial intervention allocation.

#### Primary outcome measure

This is the number of visits to health clinic during 2 years after the randomization, based on medical records, evaluated by designated assessors blinded to the intervention.

#### Secondary outcome measures

Number of episodes of acute otitis media during the 2 years after the randomization, based on medical records, evaluated by designated assessors blinded to the interventionQuality of life, measured on a 0–100 scale by the validated Otitis Media-6 questionnaire [29, 30] and the Caregiver Impact Questionnaire [31, 32], assessed at randomization, 3 months after randomization, 1 year after randomization and at the end of the trial, 2 years after randomizationNumber of episodes during the 2 years after randomization where oral or intravenous antibiotics have been administered, based on medical records, evaluated by designated assessors blinded to the interventionProportion of children with unilateral or bilateral tympanic membrane perforations in the intervention and control group at the end of the trial 2 years after randomization, based on otoscopical photos, which will be anonymized and evaluated by an ENT specialist without knowledge of the interventionSerious adverse events during the 2 years after the randomization: any adverse event that results in death, is life threatening, requires hospitalization or prolongation of existing hospitalization or results in persistent or significant disability or incapacity [33]

#### Exploratory outcomes

Number of episodes of aural discharge during the 2 years after randomization, based on medical records, evaluated by designated assessors blinded to the intervention

The primary outcome measure as well as secondary outcome measures 1 and 3 and the exploratory outcome measure will be based on medical records, while secondary outcome measure 4 will be based on clinical examination. Secondary outcome measure 2 will be based on questionnaires; the first questionnaires will be completed at the clinical examination related to randomization, the remaining questionnaires will be sent to the participants’ legal guardians by email and completed online.

### Blinding

Owing to the type of the intervention, blinding of patients, parents and caregivers is not possible. However, the outcome assessors will be blinded to intervention and we also consider the number of visits to health clinics according to medical records (the primary outcome measure) as blinded. Outcome assessors will be ENT specialists.

Blinding of the number of visits at the health-care centre is ensured by initial blinding of medical records by an investigator, and hereafter evaluation by two outcome assessors calculating the number of visits from the medical records. A third assessor may provide further evaluation in the event of any disagreement. Blinding of otoscopical results is ensured by the use of otoscopical photos, which will be anonymized and evaluated by an ENT specialist without knowledge of the intervention.

Blinding of quality-of-life measures cannot be obtained as the child and the parents are not blinded for the intervention. Therefore, this outcome measure must be considered at high risk of bias.

### Assessment of adverse events

Adverse events and adverse reactions will be assessed at every ENT visit.

### Participant discontinuation and withdrawal

Parents of participating children can withdraw their consent to participate at any time. To be able to analyze data at an intention-to-treat basis the investigator must ask for permission to use already collected data for data analysis.

The investigator or treating physician may discontinue the patient from further participation in the trial if the patient is diagnosed with any of the exclusion criteria. The investigator and treating physician will encourage the patient to continue the follow-up assessment and previously collected data should be used in further analysis.

We will monitor adherence to the control regimen. Parents of participating children will be reminded, at the time point for intervention and assessments, by email. Those who do not adhere to the control regimen specified will be further contacted by phone call and email.

### Data management

Data will be entered in the data management system Easy Trial. Easy Trial hold standards according to the Danish Data Protection Agency, i.e., data are stored on private servers. Case report forms in electronic format will be used, as well as case report forms on paper. The paper case report forms will be entered in the data management system twice by two personnel independently to promote data quality. The personnel will otherwise not be related to the trial. Patients will be identified by patient identification number, which is also used at randomization. The trial is conducted according to regulations by the Danish Data Protection Agency and only people related to the trial and the central randomization centre will have access to data.

Missing data will be minimized by checking the completed questionnaires when returned to the investigators. If there are any missing answers, the parents of the included children will emailed a request to supply the missing answers.

### Statistical plan and data analysis

Based on power (1 − *β*) = 0.80, *α* = 0.05 (two-sided) and standard deviation of five visits to health clinics andAn estimated eight visits to health clinics during 2 years in the control group andAn estimated six visits to health clinics during 2 years in the experimental group

we need a sample size of 99 individuals in each intervention group.

As we do not expect that data are normally distributed, the non-parametric van Elteren test will be used; thus, we obtain 99/0.86 = 115 participants per intervention group or 230 participants in total [34].

The two interventions will be compared regarding all outcomes. The analysis of the outcomes will be based on the intention-to-treat principle, i.e., all randomized participants will be included in the analysis, regardless of how much treatment they have received. Per-protocol analysis may be considered if important deviations from the protocol compromise the validity of the intention-to-treat analysis.

Dichotomous outcomes will be analyzed using logistic regression, continuous outcomes will be analyzed using linear regression and count data will be analyzed using the van Elteren test [34]. Our primary analysis will be adjusted for the stratification variables used in the randomization (trial site and type of otitis media). In secondary analysis, we will adjust all analyses (except when non-parametric tests are used) for additional significant design variables (age, sex, attending daycare, smokers in the household, diet, family history of otitis media). The statistical analysis will be described in detail in a separate paper published before the analysis of the trial results begins.

If only data are missing on the dependent outcome, we will use per-protocol data but we will interpret out results with caution if these missing data potentially bias our results. Otherwise, if more than 5% of the outcome data are missing, multiple imputation will be used (STATA 14). However, the 5% cut-off is not definitive. The imputation result will be considered the primary overall result. This analysis will be supplemented by the following sensitivity analyses:
**‘Best-worst-case’ scenario:** It will be assumed that all participants lost to follow-up in the experimental group have a mean score +2 standard deviations and have no event; and all those with missing outcomes in the control group have a mean score of −2 standard deviations and have an event.
**‘Worst-best-case’ scenario:** It will be assumed that all participants lost to follow-up in the experimental group have a mean score of −2 standard deviations and have an event; and all those lost to follow-up in the control group have a mean score +2 standard deviations and have no event [35].

Results from both scenarios will be presented in our trial publication.

If the null hypotheses on the primary outcome measures are not rejected, our main conclusion will be that we found no significant difference between the two interventions. The analysis of the remaining outcome measures will be presented for hypothesis-generating purposes.

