**Methods:**

The trial is an investigator-initiated, multicentre, randomized, blinded superiority trial of bilateral ventilation tube insertion versus treatment as usual (no tube) in Greenlandic children aged 9–36 months with chronic otitis media with effusion or recurrent acute otitis media. With randomization stratified by otitis media subtype and trial site, a type 1 error of 5% and a power of 80%, a total of 230 participants are needed to detect a decrease of two visits to a health clinic during 2 years, which is considered the minimal clinical relevant difference. The primary outcome measure will be assessed blindly by investigating medical records. Secondary outcome measures are number of episodes of acute otitis media, quality of life, number of episodes of antibiotics administration and proportion of children with tympanic membrane perforations.

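### The quality-of-life regression leaves out the baseline questionnaire score that is collected at randomization, which gives up precision at no saving

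*Protocol article*

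**What the plan says.** Under Secondary outcome measures, the protocol article lists quality of life, scored from 0 to 100 on the Otitis Media-6 and the Caregiver Impact Questionnaire. It is assessed at randomization, 3 months, 1 year and 2 years. Under Exploratory outcomes it adds that "the first questionnaires will be completed at the clinical examination related to randomization", while later ones are e-mailed and completed online. A baseline score is therefore planned for every child, and it is the one score obtained in person.

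The section Statistical plan and data analysis sets the model: "continuous outcomes will be analyzed using linear regression". On covariates it states "Our primary analysis will be adjusted for the stratification variables used in the randomization (trial site and type of otitis media"). The secondary analysis, except where non-parametric tests are used, adds "additional significant design variables (age, sex, attending daycare, smokers in the household, diet, family history of otitis media"). Neither list contains the baseline questionnaire score, and the section mentions neither a change score nor a repeated-measures model.

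Two further statements in the same section limit the point: "The statistical analysis will be described in detail in a separate paper published before the analysis of the trial results begins", and "The analysis of the remaining outcome measures will be presented for hypothesis-generating purposes".

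**The concern.** When an outcome scale is also measured before treatment, that first value is a natural covariate, because it can explain part of the between-child variation in the later score. The protocol article goes to the level of diet and family history in naming adjusters, yet passes over this one. The exemption for non-parametric tests does not explain the omission, because these scores are analyzed by linear regression.

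What is at stake is efficiency. Without the baseline score the residual variance is larger than it need be, so the confidence interval for the quality-of-life difference is wider. In any one trial, a chance difference between arms at baseline carries through in part to the estimated effect. These are two views of the same loss, not two separate losses.

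**Working it through.** **The plan's own figure.** The article gives no precision or power figure for quality of life. Its only calculation is for clinic visits. The inputs are a difference of 2 visits (8 versus 6), "0.05 (two-sided) and standard deviation of five visits to health clinics", and, from the abstract, "a type 1 error of 5% and a power of 80" per cent.

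- n per arm = 2 × [5 × (1.960 + 0.842) / 2]² = 98.1, rounded up to 99. The t-test version gives 99.08.
- 99 / 0.86 = 115.1, stated as 115 per arm and 230 in total.

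The figure reproduces. It concerns a different outcome, so it serves here only to supply the number per arm.

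**Effect of adding the baseline score.** Let r be the correlation between baseline and follow-up score within arm, after allowing for site and otitis type. Adding the baseline score as a covariate has these effects:

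- the residual variance is multiplied by 1 − r²;
- the standard error is multiplied by √(1 − r²);
- the precision equals that of an unadjusted trial with 115 / (1 − r²) children per arm.

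The one degree of freedom spent is ignored, as it is negligible at this size. With complete follow-up, the unadjusted difference detectable with 80% power is (1.960 + 0.842) × √(2/115) = 0.369 SD. With adjustment this is multiplied by √(1 − r²).

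The documents do not give r, so it is an assumption, shown as a range:

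| r | 1 − r² | SE reduction | Equivalent n per arm | Detectable difference (SD) | Power at 0.369 SD |
|---|---|---|---|---|---|
| 0 | 1.00 | none | 115 | 0.369 | 80.0% |
| 0.2 | 0.96 | 2.0% | 119.8 | 0.362 | 81.6% |
| 0.3 | 0.91 | 4.6% | 126.4 | 0.352 | 83.6% |
| 0.5 | 0.75 | 13.4% | 153.3 | 0.320 | 89.9% |
| 0.6 | 0.64 | 20.0% | 179.7 | 0.296 | 93.8% |

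**With drop-out.** Attrition worsens the absolute figures but not the proportional gain. With an assumed 20% loss (115 × 0.8 = 92 per arm), the detectable difference is 0.413 SD unadjusted and 0.358 SD at r = 0.5. The ratio is again 0.866.

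**Chance imbalance.** With 115 per arm, the baseline difference between arms has a standard error of √(2/115) = 0.132 SD. An imbalance of that size shifts the unadjusted follow-up difference by r × 0.132 SD, which is 0.066 SD at r = 0.5. Adjustment removes this shift.

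**The case against.** The strongest reply is that the covariate rule is generic. It covers all outcomes at once, nothing in it says that no other variable may be used, and the next sentence defers detail to a separate statistical paper. A baseline value of the same scale exists only for the questionnaires, so its inclusion could be seen as detail for that paper. This lowers confidence and severity, since the paper may well add the covariate. It does not remove the point: the article does not leave covariates open but names them for both analyses, and a paper that follows those lists would omit the baseline score.

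The size is also open to challenge. It rests wholly on r, and a low value is plausible over 2 years in very young children. At r = 0.2 the gain in standard error is only 2%. That objection stands, and it is why a range is given.

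A reader might be tempted by two stronger readings, and the article supports neither.

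- One is that each follow-up time is analyzed by its own separate regression. The article names linear regression and does not say how the three follow-up times are handled.
- The other is that a child who misses the 2-year questionnaire contributes nothing, so that the omission adds missing-data bias. The same section provides for multiple imputation when more than about 5% of outcome data are missing, takes the imputed result as the primary overall one, and adds best-worst and worst-best scenarios. Nothing keeps earlier scores out of the imputation model. A preceding clause on data missing only for the dependent outcome may point to a non-imputed analysis, but how that clause should be read is a different question.

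**Conclusion.** The point holds as a matter of precision. Followed as written, the plan gives a quality-of-life estimate that is unbiased by virtue of randomization but less precise than the data allow. For an assumed within-arm correlation of 0.2 to 0.6, baseline adjustment would reduce the standard error by about 2% to 20%. At 0.5 the reduction is 13%, worth the same as raising 115 per arm to about 153. At 0.2 to 0.3 the gain is small, and from about 0.5 it is material.

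The reach is narrow. Quality of life is a secondary, hypothesis-generating outcome. The Blinding section already rates it at high risk of bias because the families are unblinded, and baseline adjustment does nothing about that. The primary outcome, its van Elteren test and the sample size of 230 are untouched. This is a free improvement of minor to moderate weight, not an error that threatens the trial's main conclusion.

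**What to change.** In the statistical paper, add one sentence: in the primary analysis, each follow-up Otitis Media-6 and Caregiver Impact score is regressed on treatment arm, trial site, otitis type and the baseline score of the same questionnaire. The secondary analysis keeps the baseline score and adds the variables already listed. State also that the baseline score used is the one completed before the parents learn the allocation. The article places it at the randomization examination without giving the order.

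A mixed model over all follow-up times with the baseline score as covariate would also serve, but it is one of several reasonable choices and is not required to meet this point.

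The cost is one or two sentences. The baseline questionnaire is already scheduled, and no extra visit, data item or participant is needed. The change should be fixed before the analysis of the results begins, which is when the article says the statistical paper will be published.

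### The best-worst and worst-best missing-data scenarios run the wrong way for the primary outcome, where more visits is worse, and they impute negative visit counts

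*Protocol article*

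**What the plan says.** The protocol article, Statistical plan and data analysis, supplements multiple imputation with two extreme scenarios. In the best-worst case it is assumed that "all participants lost to follow-up in the experimental group have a mean score +2 standard deviations and have no event", while controls with missing outcomes get mean −2 SD and an event. In the worst-best case it is assumed that "all participants lost to follow-up in the experimental group have a mean score of −2 standard deviations and have an event", while lost controls get mean +2 SD and no event. The results of both are to be published. No separate rule is given for counts, and no lower limit is set on imputed values.

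On the primary outcome, the section Primary outcome measure states: "This is the number of visits to health clinic during 2 years after the randomization". The abstract (Methods) gives the direction of benefit: the sample is the number "needed to detect a decrease of two visits to a health clinic during 2 years". The planning figures are 8 visits in the control group, 6 in the tube group and a "standard deviation of five visits to health clinics".

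**The concern.** Pairing +2 SD with no event, and −2 SD with an event, only makes sense if a high value is good. For clinic visits a high value is bad. The same holds for the other counts: episodes of acute otitis media, episodes of antibiotic treatment and, among the exploratory outcomes, episodes of aural discharge. Followed literally, the scenario meant to favour tubes gives lost tube children very many visits and lost controls very few. Under the same label, binary outcomes such as perforation move in favour of tubes. One label therefore points in two directions.

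The worst-best case is the stress test of a claimed benefit. If the paper reported that a reduction in visits survives it, the reader would in fact be looking at the assumption most favourable to tubes. Separately, subtracting two SDs from the planned means gives fewer than zero visits.

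**Working it through.** **Inputs.** From Statistical plan and data analysis: control mean 8, tube mean 6, SD 5, two-sided α 0.05, power 0.80. From Randomization: 1:1 allocation. The article gives no dropout rate, so the share missing, d, is an assumption; it is taken as equal in both arms and varied from 5% to 20%. The article does not say whose mean is used for imputation. Own-arm means are used first, then the pooled mean.

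**Check of the planning figures.** n per arm = 2(1.960 + 0.842)² × 5² / 2² = 98.1, so 99; the t-test version gives 99.08. Then 99/0.86 = 115.1. The plan's 99, 115 and 230 are reproduced (rounding up would give 116 and 232), so the means and SD can be relied on as the plan's own.

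**Imputed values as written** (2 SD = 10 visits):
- Best-worst: tubes 6 + 10 = 16; control 8 − 10 = −2.
- Worst-best: tubes 6 − 10 = −4; control 8 + 10 = 18.

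Both −2 SD values are negative. To avoid this the SD would have to be at most 8/2 = 4 in the control group and 6/2 = 3 in the tube group.

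**Difference in mean visits, tubes minus control** (complete data: 6 − 8 = −2; negative favours tubes):

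difference = (1 − d)(−2) + d × (imputed tubes − imputed control)

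- As written, best-worst: (1 − d)(−2) + 18d = −2 + 20d
- As written, worst-best: (1 − d)(−2) − 22d = −2 − 20d
- Signs corrected and counts floored at 0, best-worst (tubes 0, control 18): (1 − d)(−2) − 18d = −2 − 16d
- Signs corrected and counts floored at 0, worst-best (tubes 16, control 0): (1 − d)(−2) + 16d = −2 + 18d

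| Assumed loss per arm | As written: best-worst | As written: worst-best | Corrected: best-worst | Corrected: worst-best |
|---|---|---|---|---|
| 5% | −1.0 | −3.0 | −2.8 | −1.1 |
| 10% | 0.0 | −4.0 | −3.6 | −0.2 |
| 15% | +1.0 | −5.0 | −4.4 | +0.7 |
| 20% | +2.0 | −6.0 | −5.2 | +1.6 |

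At every loss rate the scenario labelled best moves the result against tubes, and the one labelled worst moves it in their favour.

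**Pooled mean of 7 instead of own-arm means.** Imputed values become 17 and −3. As written, best-worst / worst-best are +0.2 / −3.8 at 10% loss and +2.4 / −5.6 at 20%. The conclusion does not change.

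**The case against.** - **The rule speaks of scores and events, not counts.** The only outcome on a score-type scale is quality of life (0–100), so this may be generic wording that was never adapted. That is plausible, and the event half shows what was intended. But the text does not limit the rule to such scales, and no other rule covers the counts.
- **The analysis is supplementary and both bounds are published.** The imputation result is the primary one, and swapping labels leaves the same pair of results. This stands and limits the damage: the range is not lost, only its interpretation. A careful reader might notice that the best case worsened the result for tubes.
- **The scenarios may not be reached for the primary outcome.** If only the dependent outcome is missing, the plan first turns to per-protocol data. Also, visits come from medical records, so a family that stops attending need not have a missing count. Both are fair points. Still, the article says without qualification that both scenarios will be presented, and its Discussion expects dropout, including through migration.
- **Counts are analysed with the van Elteren test, which uses ranks.** The mean differences above illustrate direction and size; they are not outputs the plan specifies for counts. In a rank test a negative value is merely the lowest rank, so the negative values matter mainly for reported means. The reversal remains, because lost tube children are still placed at the wrong end of the ranking.
- **A detailed analysis paper is promised before analysis.** That is a suitable place for the correction. It does not make the stated rule right.

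**Conclusion.** The concern holds. For the primary outcome and the other counts the two scenario labels are reversed, while the event half of the same rule is correctly oriented. With the plan's own means and SD, own-arm imputation and an assumed equal loss of 10% per arm, the labelled best case gives 0.0 and the labelled worst case −4.0 visits; at 20% they give +2.0 and −6.0. With the signs corrected and counts floored at 0, the true worst case at 20% is +1.6, a result against tubes. Imputed values of −2 and −4 visits follow from the planning figures; the actual values will depend on the observed means and SDs.

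The reach is limited to a sensitivity analysis and its interpretation. The sample size, the primary test and the primary imputation result are untouched. For the questionnaires the rule cannot be checked, because the article does not state which end of the 0–100 scale is better.

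**What to change.** Replace the two scenario definitions with ones based on benefit, outcome by outcome:

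- **Counts** (visits, acute otitis media, antibiotic episodes, aural discharge): best-worst puts lost tube children at mean −2 SD and lost controls at mean +2 SD; worst-best is the mirror image. Floor imputed values at 0. A cap at the highest observed count is optional.
- **Binary outcomes**: keep the present rule.
- **Questionnaire scores**: state which direction is better, apply the signs accordingly and keep values within 0–100.
- State whose mean and SD are used (own arm or pooled).

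The cost is one paragraph, in the protocol or in the announced analysis paper. It needs no new data and no change to the sample size. It should be done before outcome data are seen, so that the relabelling cannot look data-driven.
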